### Exclusion criteria

Participants meeting any of the following criteria will be excluded from the study: pregnant or breastfeeding; woman of child-bearing age during the study period; patients who had received medicine or acupuncture therapy in other hospitals before this study; diabetes course ≥ 5 years, grade 3 hypertension or hyperlipidemia ≥ 3 years; history of malignant tumors, sexually transmitted disease, chronic renal or hepatic disease, glaucoma, acute otitis, ipsilateral chronic otitis, tuberculosis, immunodeficiency syndromes, recent head injury, psychiatric disease, infectious diseases, or any other conditions that present risk of being influenced by the study treatment or that may affect the completion of the study; and patients participated in other clinical trials within three months.

### Randomization and blinding

Figure 2 illustrates the schedule of enrolment, allocation, interventions, and assessments in this trial. The enrolled participants will be randomly assigned to group A, B, or C (1:1:1). An independent statistician will generate the block randomization scheme in a blinded manner. The table will be managed by another independent researcher who is not involved in the recruitment, acupuncture treatment, or assessment. The CRC will send the assignment information to the researcher who will conduct the random allocation; subsequently, the researcher will only provide assignment information to the doctors of TCM, who will perform the acupuncture treatment. In order to ensure concealing of the allocation, the information will be recorded in an allocation log by the researcher and not opened until the data are locked. The participants will be blinded to the type of acupuncture treatment; the assessor, data managers, statisticians, and study monitors will be blinded to the allocation. The blinding will be maintained until the data are locked. For evaluation in a blinded manner, the allocation guessing will be assessed immediately after the final treatment. The practitioners and assessors will be instructed to treat the participants according to the predefined standard operating procedures (SOPs) during the trial to maintain blinding; un-blinding will be considered only in the case of rights and safety of the participants, including the occurrence of serious adverse effects (SAEs). In such cases, the researchers will notify the principal investigator (PI) and document the subsequent processes.

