### Design and setting

This study is a single-center, three-arm, patient-blinded and assessor-blinded (to the type of acupuncture treatment), parallel-group, RCT conducted in China. The results followed the Consolidated Standards of Reporting Trials (CONSORT) guidelines as well as Standards for Reporting Interventions in Clinical Trials for Acupuncture (STRICTA) [20] and Standard Protocol Items: Recommendations for Interventional Trials (SPIRIT) guidelines [21]. This study (protocol version 1.0, 30 June 2017) has been registered at the Chinese Clinical Trials Registry (ChiCTR-INR-17012955). Figure 1 shows the research design and Additional file 1 displays the complete SPIRIT checklist.

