### Methods of recruitment

A total of 99 participants diagnosed with Bell’s palsy and mainly suffering the symptom of hypophasis through the outpatient or inpatient department will be recruited at the Department of Acupuncture, Neurology, and Geratology, Baoshan Hospital of Integrated Traditional Chinese Medicine and Western Medicine, Shanghai. The participants will be recruited by posters displayed in the hospital registration hall and brochures sent out to the visitors of those departments. The study title, research target, period, location, and contents of the intervention will be introduced to the participant.

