### Study setting

The research assistants will obtain written consent (version 1.0, 30 June 2017) from the patients potentially eligible for the study. A researcher will explain the manipulation of acupuncture treatments used in traditional Chinese medicine (TCM) clinics. Subsequently, a researcher will screen whether the patient can participate in the study. If the patient fulfills the inclusion/exclusion criteria, a clinical research coordinator (CRC) specified by the scientific research department, Baoshan Hospital of Integrated Traditional Chinese Medicine and Western Medicine, Shanghai will contact an independent researcher who has the random number table; the participants will be randomly allocated into one of the three groups (group A, B, or C) at a 1:1:1 allocation ratio. All participants will receive conventional acupuncture therapy; however, the participants assigned to group A will be given additional acupuncture on the acu-point Bi’nao, while the participants assigned to group B will be given extra acupuncture on a point 1 cm backward to Bi’nao as a placebo point. Only group C participants will not receive extra acupuncture on any other acu-point.

The participants of this trial will undergo acupuncture treatments three times a week for one month. The Eye Crack Width Measurement (ECWM) and Eyelid Strength Assessment (ESA) of all the participants will be performed at the allocation time point, weekly during the treatment duration, and one month after the first therapy. The first ECWM and ESA value will be recorded as a baseline and the final values will be recorded as the end-time measurement. The follow-up visits for all participants will be scheduled at three months after the first acupuncture therapy. After the participants have completely recovered from hypophasis, the acupuncture therapy will be stopped and the final ECWM and ESA values will be recorded as an end-time measurement.

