All patients from the three groups will undergo acupuncture therapy at Cuanzhu (BL2), Yangbai (GB14), Sizhukong (SJ23), Shangming, Waiguan (SJ5), and Zhaohai (KI6) points (Fig. 3) as basic therapy. The acu-points are identified by the Method of Point Location issued by the World Health Organization (WHO). The acupuncture needles will be inserted straightly or obliquely at a depth of 10–30 mm to effectuate the desired sensation of “De qi” (Table 2) by reinforcing-reducing techniques of lifting, thrusting, twisting, and rotating the needles moderately. When the acupuncture doctor feels sinking, astringent, and tightness around the needle by his/her finger while the patient senses soreness, numbness, distension, and heaviness around the acu-point, this will be considered the arrival of the “De qi” sensation [22]. All the needles will be retained for 20 min. The acupuncture therapy will be performed three times each week on Monday, Wednesday, and Friday. Consequently, the participants in Group A (real acu-point group) will receive extra manual acupuncture therapy at Bi’nao (LI14) and participants in Group B (sham acu-point group) will receive extra manual acupuncture therapy three times a week as Group A but 1 cm backward to Bi’nao (Fig. 3) as a placebo point. Participants in Group C will receive no extra acupuncture therapy except basic therapy. The treatment will be performed for one month and all the participants will be reminded of the next visit by researchers.

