### Outcome measures

#### Primary outcome

ECWM will be performed using a graduated ruler to measure the width (mm) between the upper and lower eyelids when the patients attempt to close his eyes. The measurements will be taken three times and the average recorded. ECWM will be performed before acupuncture therapy as the primary time measurement, weekly during the treatment duration, and at the first month after the first therapy by three physicians, and the average value recorded. The mean value and standard deviation among the participants in every group will be calculated; the differential values of eye crack width (mm) between the intervention and control groups will be compared.

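### Participant blinding is claimed for all three arms, but only Bi'nao versus sham (A–B) has a matching needle; A–C and B–C have no credible participant blinding

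*Protocol article*

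**What the plan says.** Under Design and setting, the trial is described as a "three-arm, patient-blinded and assessor-blinded (to the type of acupuncture treatment), parallel-group, RCT conducted in China". Under Randomization and blinding, the claim is repeated for participants ("The participants will be blinded to the type of acupuncture treatment"), and the same sentence adds that "the assessor, data managers, statisticians, and study monitors will be blinded to the allocation". Neither section sets Group C apart.

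The arms are described under Study setting and Acupuncture treatment. All three receive the same basic points. Group A adds Bi'nao (LI14), Group B adds a point 1 cm from it, and for the third arm: "Participants in Group C will receive no extra acupuncture therapy except basic therapy". Study setting says the same: "Only group C participants will not receive extra acupuncture on any other acu-point".

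Under Methods of recruitment: "The study title, research target, period, location, and contents of the intervention will be introduced to the participant". The article's title names Bi'nao.

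The primary outcome, ECWM, uses a ruler to "measure the width (mm) between the upper and lower eyelids when the patients attempt to close his eyes". The secondary outcome, ESA, grades the strength of eyelid closure against the healthy side. The stated check on blinding is that "the allocation guessing will be assessed immediately after the final treatment".

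**The concern.** A sham needle blinds only those arms that receive a needle in that place. Group C has none, and its patients have been told what the trial adds. A patient who knows that the tested component is absent may expect less and try less hard, and one who receives it may do the opposite. A blinded assessor holding the ruler cannot remove an effect that acts through the patient's own effort.

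This matters because the Objective names two comparators side by side: the sham point and no needling at Bi'nao. The Statistical analysis section tests the three groups together by one-way ANOVA (or Kruskal–Wallis). A difference driven by Group C could then be reported, under the blanket label, as patient-blinded evidence that Bi'nao itself augments recovery.

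**Working it through.** **1. Needle count.** Inputs are the points in Tables 1 and 2 and under Acupuncture treatment. Unilateral basic points: BL2, GB14, SJ23 and Shangming, so 4. Bilateral basic points: SJ5 and KI6, so 2 × 2 = 4.

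- Group C: 4 + 4 = 8.
- Groups A and B: 8 + 1 = 9.

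This reproduces the 8–9 insertions per session in Table 1. SJ5 lies on the forearm (Fig. 3 legend), so Group C does have arm needles. What it lacks is the upper-arm needle at or near Bi'nao. For LI14, Table 2 gives perpendicular insertion at 20–30 mm, and Table 1 gives De qi as the response sought and 12 planned sessions.

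**2. Which contrasts the sham can blind for participants.**

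| Contrast | Upper-arm needle | Participant blinding supported? | Assessor blinding stated? |
|---|---|---|---|
| A–B | both arms | yes, in principle | yes |
| A–C | A only | no | yes |
| B–C | B only | no | yes |

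Two of three contrasts are affected, and 33 of 99 patients are in the arm without a counterpart needle.

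One row of Table 1 (setting and context of treatment) says that the control group will receive the same treatment as the acupuncture group after first-week evaluations. That conflicts with the two sections describing Group C and must be reconciled. The table above takes Group C as those two sections describe it.

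**3. Could the size be calculated?** Only as an illustration. The design inputs come from Sample size calculation: SDs of change 1 and 3, difference 2, two-sided α 0.05, power 90%.

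- Plan's own figure: (1.96 + 1.28)² × (1² + 3²) / 2² = 26.24, so 27 per group; 27 × 1.2 = 32.4, so 33; 3 × 33 = 99. Reproduced.
- Assume that Bi'nao has no effect, that one point is 1 mm, and that expectation alone shifts A–C by b mm. The two-sided rejection probability is Φ(b/SE − 1.96) + Φ(−b/SE − 1.96).
- At 27 per arm, SE = √(10/27) = 0.609. For b = 0.25, 0.5 and 1.0 this gives 7.0%, 13.0% and 37.6%, against 5% at b = 0.
- At 33 per arm, SE = √(10/33) = 0.550, giving 7.4%, 14.9% and 44.3%.
- The unequal SDs are hard to justify if Bi'nao does nothing. At 27 per arm with both SDs 3, SE = √(18/27) = 0.816, giving 9% at 0.5 mm and 23% at 1.0 mm. With both SDs 1, SE = √(2/27) = 0.272, giving 45% and 96%.

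At 0.5 mm the answer thus runs from 9% to 45% with the choice of SD alone, and no figure in the document supports any value of b. The calculation also models a pairwise test, whereas the article names a three-group test. It shows the direction of the risk, not its amount.

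**4. Timing of the guess.** Study setting stops treatment once hypophasis has fully recovered, so for such a patient the last session falls at about the time of recovery. A guess taken only then may reflect whether the eye closes as much as what the patient could tell about the needle.

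**The case against.** The strongest reply is that the label is qualified. Participants are said to be blinded to the type of acupuncture treatment, whereas assessors and others are said to be blinded to the allocation. That may mean real versus sham only, which is all the design can deliver. This is a fair reading, but neither section says so or excepts Group C, so a clarification is still needed.

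The design is also defensible. An add-on arm, a sham arm and a no-add-on arm form a recognised combination: A–C gives the total effect and A–B the specific one. The Background says the trial was designed to compare with a placebo point, and nothing in the article says that A–C alone will carry a Bi'nao-specific claim. This stands, and it is why the remedy is to label the contrasts rather than redesign the trial.

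Three stronger readings are tempting and are not supported:

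- **A–C is open-label.** It is not: the assessor, data managers, statisticians and monitors are blinded.
- **Group C patients cannot be blind, or know their arm from the first session.** The consent text is not shown, the recruitment section does not say that the location of Bi'nao is disclosed, and a lay patient might take a forearm needle for it. Table 1 also says that all participants are told they will receive potentially helpful acupuncture. What can be said is that no credible basis for blinding is given.
- **The end-of-treatment guess is worthless, or uninformative in Group C.** It is a legitimate check, and in Group C it would show directly whether patients knew their arm. Its weakness is only that it is mixed with outcome.

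**Conclusion.** The point holds as a limit on the blinding claim. As written, participant blinding covers three arms; the design supports it for A versus B alone. A–C and B–C are assessor-blinded without credible participant blinding, on two outcomes that depend on the patient's effort. This affects 33 of 99 patients and two of three contrasts.

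The conclusion rests on the needle lists and on the statement that title and intervention contents are disclosed. That expectation alters closure effort is a plausible mechanism, not something the document demonstrates. A reader might infer a definite false-positive rate, such as 13% or 38%, from the illustration; those values rest on assumed shifts and unequal SDs and should not be cited as the size of the problem. The A–B contrast is not impaired by this point.

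**What to change.** 1. Under Design and setting and under Randomization and blinding, state participant blinding for A versus B only, and describe A–C and B–C as assessor-blinded but not participant-blinded.
2. State that a claim of a Bi'nao-specific effect rests on A–B, with A–C read as the total add-on effect and supportive.
3. For patients still to be enrolled, ask the allocation guess after the first session as well as after the last, and report it by arm.

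The cost is two wording changes, one added statement and one extra question, with no additional patients and no change to treatment. The downsides are that A–C openly becomes a weaker comparison, and that early guesses will be missing for those already treated, since the Trial status section reports recruitment as ongoing. Neutral naming of the point in participant material is optional; introduced mid-recruitment, it would leave earlier and later patients told different things.

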**Fig. 2 Fig2:**
[figure not shown]
The Standard Protocol Items: Recommendations for Interventional Trials (SPIRIT) Figure. The schedule of enrollment, allocation, interventions, and assessments. ECWM Eye Crack Width Measurement, ESA Eyelid Strength Assessment

### Intervention

#### Acupuncture treatment

Acupuncture will be performed by specialists in TCM and follow the STRICTA 2010 checklist (Table 1).

**Table 1 Tab1:** Details of acupuncture intervention (according to the Standards for Reporting Interventions in Clinical Trials of Acupuncture (STRICTA) 2010 guidelines Expansion of Item 5 from Consolidated Standards of Reporting Trials 2010 guidelines)

Acupuncture rationale	Style of acupuncture	Traditional Chinese Medicine
	Rationale for treatment	Acupuncture has been historically used to treat hypophasis in facial palsy. Additionally, it is known to be a safe treatment used in a wide range of symptoms caused by Bell’s palsy
	Extent to which treatment varied	The participants in the intervention group all receive the same manual acupuncture treatment
Details of needling	Number of needle insertions per individual per session	8–9
	Names of the insertion points (uni/bilateral)	BL2, GB14, SJ23, Shangming, LI14 (unilateral, affected side); SJ5, KI6(bilateral)
	Depth of insertion	10–30 mm (exact depth shown in Table 2)
	Response sought	De-qi
	Needle stimulation	Manual stimulation (exact details are in the text)
	Needle retention time	20 min
	Needle type	0.30 mm (diameter) × 25 mm (length) disposal needle (Huatuo Acupuncture Inc., Suzhou, China)
Treatment regimen	Number of treatment sessions	12
	Frequency and duration of treatment sessions	3 sessions per week for 4 weeks
Other components of treatment	Details of other interventions administered to the acupuncture group	No other interventions are done
	Setting and context of treatment	All participants are informed that they will receive acupuncture treatment, which can potentially reduce symptoms of hypophasis; however, the control group will have to complete the evaluations during the first week before receiving the same treatment as the acupuncture group
Practitioner background	Description of participating acupuncturists	Specialists in TCM with at least 3 years of practice in acupuncture
Control or comparator interventions	Rationale for the control or comparator in the context of the research question	Sham acu-point is used as a placebo control
	Precise description of the control or comparator	Placebo control group be given extra acupuncture on a point 1 cm backward to Bi’nao as a placebo point

All patients from the three groups will undergo acupuncture therapy at Cuanzhu (BL2), Yangbai (GB14), Sizhukong (SJ23), Shangming, Waiguan (SJ5), and Zhaohai (KI6) points (Fig. 3) as basic therapy. The acu-points are identified by the Method of Point Location issued by the World Health Organization (WHO). The acupuncture needles will be inserted straightly or obliquely at a depth of 10–30 mm to effectuate the desired sensation of “De qi” (Table 2) by reinforcing-reducing techniques of lifting, thrusting, twisting, and rotating the needles moderately. When the acupuncture doctor feels sinking, astringent, and tightness around the needle by his/her finger while the patient senses soreness, numbness, distension, and heaviness around the acu-point, this will be considered the arrival of the “De qi” sensation [22]. All the needles will be retained for 20 min. The acupuncture therapy will be performed three times each week on Monday, Wednesday, and Friday. Consequently, the participants in Group A (real acu-point group) will receive extra manual acupuncture therapy at Bi’nao (LI14) and participants in Group B (sham acu-point group) will receive extra manual acupuncture therapy three times a week as Group A but 1 cm backward to Bi’nao (Fig. 3) as a placebo point. Participants in Group C will receive no extra acupuncture therapy except basic therapy. The treatment will be performed for one month and all the participants will be reminded of the next visit by researchers.

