**Fig. 3 Fig3:**
[figure not shown]
Location of acupoints. BL2, Cuanzhu, on the medial end of the eyebrow; GB14, Yangbai, directly above the pupil, 1 cun above the midpoint of the eyebrow; Shangming, in the orbital cavity and at the midpoint of the orbital margin; SJ23, Sizhukong, in the depression at the lateral end of the eyebrow; LI14, Bi’nao, at the stop of deltoid muscle on the line between LI15 (Jianyu) and Quchi (LI11), 7 cun above Quchi (LI11); Sham LI14, 1 cm backward to Bi’nao; SJ5, Waiguan, on the line joining Yangchi (SJ4) and the tip of elbow, 2 cun above the dorsocarpal transverse crease between the ulna and radius; KI6, Zhaohai, in the depression directly below the tip of the medial malleolus

**Table 2 Tab2:** Acu-points and needle insertion procedure

Acupuncture point	Direction	Depth (mm)
BL2 (Cuanzhu, affected side)	Transversely, along with geisoma	5–10
GB14 (Yangbai, affected side)	Transversely, toward geisoma	5–10
SJ23 (Sizhukong, affected side)	Obliquely toward partes temporalis	5–10
Shangming (affected side)	Transversely, along with gap between the eye socket and the eyeball	5–10
LI14 (Bi’nao, affected side)	Perpendicular to the skin	20–30
SJ5 (Waiguan, bilateral)	Perpendicular to the skin	10–20
KI6 (Zhaohai, bilateral)	Perpendicular to the skin	5–10

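### The general needle depth of 10–30 mm does not match the point-by-point depths in Table 2, and part of the Bi'nao range exceeds the specified 25 mm needle

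*Protocol article*

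**What the plan says.** The Acupuncture treatment section names the six basic points needled in every arm and continues: "The acupuncture needles will be inserted straightly or obliquely at a depth of 10–30 mm". The same sentence cites Table 2.

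Table 1 gives the depth of insertion as "10–30 mm (exact depth shown in Table 2" and specifies one needle type, "0.30 mm (diameter) × 25 mm (length) disposal needle".

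Table 2 sets a direction and a depth for each point. Shangming reads "Transversely, along with gap between the eye socket and the eyeball 5–10", BL2 reads "Transversely, along with geisoma 5–10" and GB14 reads "Transversely, toward geisoma 5–10". SJ23 (oblique) and KI6 (perpendicular) are also at 5–10 mm, SJ5 is at 10–20 mm, and Bi'nao (LI14) is perpendicular at 20–30 mm. The Fig. 3 legend places the orbital point: "Shangming, in the orbital cavity and at the midpoint of the orbital margin".

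Table 2 has no row for the sham point. The text describes the extra needling in Group B by reference to Group A, with the location moved by 1 cm.

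**The concern.** A summary range should contain the values it summarises, and this one leaves out everything Table 2 lists below 10 mm. For five of the seven points, the lower limit of the general range is the upper limit in Table 2. Four of those five (BL2, GB14, SJ23, Shangming) lie on the forehead or around the eye, and all five are needled in every arm. Someone working from the general sentence could go deeper than Table 2 at those points, and could use a direction other than the one Table 2 gives at BL2, GB14 and Shangming. This bears on participant safety while recruitment is ongoing (Trial status).

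The needle length is a separate matter. Bi'nao is the point that distinguishes the experimental arm. If part of its listed depth is longer than the needle, that part of the experimental treatment cannot be given as described.

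**Working it through.** No sample-size or power formula applies. The check compares stated figures.

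**Inputs.** General range 10–30 mm (text and Table 1); needle length 25 mm (Table 1); depths and directions by point (Table 2); sides needled (Tables 1 and 2).

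| Point | Needles | Direction (Table 2) | Depth (Table 2) | Overlap with 10–30 mm |
|---|---|---|---|---|
| BL2 | 1 | transverse | 5–10 mm | 10 mm only |
| GB14 | 1 | transverse | 5–10 mm | 10 mm only |
| SJ23 | 1 | oblique | 5–10 mm | 10 mm only |
| Shangming | 1 | transverse | 5–10 mm | 10 mm only |
| KI6 | 2 | perpendicular | 5–10 mm | 10 mm only |
| SJ5 | 2 | perpendicular | 10–20 mm | all |
| LI14 (Bi'nao) | 1 | perpendicular | 20–30 mm | all |

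**Number of insertions.** Basic points: 1 + 1 + 1 + 1 + 2 + 2 = 8. With LI14: 8 + 1 = 9. Table 1's figure of 8–9 per session is reproduced, so the rows are complete for Groups A and C.

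**General range.** Over all seven points, the smallest lower limit is 5 mm and the largest upper limit is 30 mm, giving 5–30 mm. Over the six basic points it is 5–20 mm. The stated 10–30 mm is reproduced by neither.

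**Extent.** The five points at 5–10 mm account for 1 + 1 + 1 + 1 + 2 = 6 insertions: 6 of 9 in Group A and 6 of 8 in Group C. They are scheduled for all 99 planned participants at up to 12 sessions.

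**Largest possible excess over Table 2 at those points.** On paper it is 30 − 10 = 20 mm. The needle limits insertion to 25 mm, so it is 25 − 10 = 15 mm.

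**Bi'nao against the needle.** 30 − 25 = 5 mm of the range lies beyond the needle. The range is 30 − 20 = 10 mm wide, so 20–25 mm (half) is within the needle's length and 25–30 mm (half) is not. LI14 is the only point whose Table 2 range exceeds 25 mm. Table 1 has the same conflict within itself: a depth of up to 30 mm with a 25 mm needle.

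**Direction.** The text allows straight or oblique insertion. Table 2 gives transverse insertion for three of the seven points.

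**The case against.** The strongest reply is that Table 2 governs. The general sentence cites it, and Table 1 names it as the place for exact depths. A single range for points from the forehead to the ankle cannot serve as an instruction for each point, and the needling is done by specialists with at least 3 years of practice who are trained before the trial. This stands in part: it makes Table 2 the probable intended source and a misapplication less likely. It does not make the lower limit of 10 mm correct as a summary of Table 2. Nor does it settle the needle conflict, because the 30 mm figure is in Table 2 itself.

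A reader might infer more than the documents support:

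- *That all three places disagree with one another.* On depth, the text and Table 1 agree. Only Table 2 differs.
- *That needling could go 20 mm too deep by Table 2's limits.* The specified needle rules that out; 15 mm is the most.
- *That the experimental treatment cannot be reproduced.* Half of the Bi'nao range is within the needle's length, and needling is guided by a defined response (De qi).
- *That the sham needling is undefined.* Its location is given and its delivery is tied to that of Group A. A row in Table 2 would be clearer, but its absence is not a contradiction.
- *That the operating procedures and training carry the error.* They are not shown, and nothing indicates that they do.
- *That the comparison between arms is biased.* The five conflicting points are basic therapy common to all arms, so the conflict by itself creates no difference between them.

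**Conclusion.** The point holds in two parts. First, the general depth and direction statement does not match the table it refers to: five of seven points overlap it only at 10 mm, and three have a direction that it omits. As written, it would permit up to 15 mm more than Table 2 at points around the eye, in all three arms. Second, the upper 5 mm of the 10 mm-wide Bi'nao range cannot be delivered with the needle specified.

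Both figures assume that the whole 25 mm of needle can be inserted. If some must stay outside the skin, the 15 mm falls and the 5 mm rises. They also assume that the 25 mm needle is used at every point, as Table 1 implies by naming no other.

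These are errors of stated fact, not gaps left by condensing a protocol into an article. They touch safety near the eye and the description of the experimental needling. They do not touch the sample size or the analysis.

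**What to change.** The responsible clinicians should:

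1. Reconcile the general sentence, the depth entry in Table 1 and the rows of Table 2, so that each point has one depth and one direction and any summary range follows from them.
2. Reconcile the Bi'nao depth range with the needle specification.
3. Check that the operating procedures and training material agree with the reconciled text, and tell the acupuncturists if anything changes.

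Adding a row for the sham point to Table 2 is an optional clarification. It would show directly that Groups A and B differ only in location.

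The cost is an edit to one sentence and a few table cells, plus a document check. This review does not say which depth, direction or needle is right.
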